## Methods/design

### Study setting

This is a two-armed parallel randomized controlled trial that will be conducted among overweight, pregnant women receiving prenatal care in seven Primary Health Units of Ribeirão Preto, SP, Brazil: Waldemar Barnsley Pessoa (Parque Ribeirão), [name] Sahão (Vila Virgínia), [name] da Costa Moraes (Jardim Presidente Dutra), Adalberto Texeira Andrade (Vila Recreio), Carlos Chagas (Vila Abranches), Rubens Issa Halak (Jardim Juliana) and Dr. Ítalo Baruffi (Castelo Branco). The Primary Health Units were selected according to the high demand for prenatal care and the minimum infrastructure necessary to conduct the study.

The study has been approved by the Research Ethics Committee of the School Health Centre of the Ribeirão Preto Medical School, University of São Paulo. Ribeirão Preto, SP, Brazil, (69,997,717.6.0000.5414, and 97,288,818.0.0000.5414).

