### Sample size

The sample size calculation was based on the primary outcome of the study. A 20% difference in the proportion of adequacy of weight gain between the treatment groups is expected [42]. Considering a minimum significance level of 5% (α = 0.05) and a power of 90% (β = 0.1), with a 20% loss during monitoring, a sample of 300 women will be sufficient.

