### Allocation

The eligible pregnant women that agree to participate in the study will be randomly allocated to the treatment groups. Randomization will be performed directly using the Research Electronic Data Capture (REDCap) software [43, 44], with a spreadsheet of numbers randomly generated by Microsoft Office Excel. Stratification between the groups will be performed considering the prenatal care Health Unit, which may differ in relation to the quality of the prenatal care offered and the socioeconomic profile of the users. Given the nature of the intervention, both the study participants and the researchers will be aware of the group allocation.

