### Statistical analyses

The analyses of this study will follow the intention to treat principles. The homogeneity of the sample at the beginning of the study will be verified using Student’s t-test for independent variables or the Mann-Whitney U test, depending on the data distribution, for the continuous variables; and the X^2^ test for categorical variables. For the continuous variables the delta will be calculated and differences with the baseline will be tested using Student’s t-test for dependent variables or the Wilcoxon test. The impact of the intervention on the proportion of women with appropriate weight gain will be assessed by means of the relative risk and 95%CI adjusted for confounding factors.

The statistical correlation method will be used to investigate the impact of the intervention on neonatal adiposity and birth weight. If there is linearity between the treatment group data and outcomes, linear regression models will be employed, adopting adiposity and birth weight as the dependent variables, adjusted for potential confounders.

The analyses will be conducted using the SPSS® software (version 24) and *p* values < 0.05 will be considered significant.

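### The primary analysis does not name Health Unit, the randomisation stratum, and leaves its adjustment set open; naming both is a free improvement

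*Protocol article*

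**What the plan says.** The Allocation section of the protocol article fixes the stratification: "Stratification between the groups will be performed considering the prenatal care Health Unit". It gives the reason in the same sentence, saying of the units: "which may differ in relation to the quality of the prenatal care offered and the socioeconomic profile of the users". The Study setting section puts their number at seven. Allocation also says that neither the participants nor the researchers are blinded.

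The Statistical analyses section describes the primary comparison of appropriate weight gain as a "relative risk and 95%CI adjusted for confounding factors". It lists no covariates, does not mention Health Unit, and gives no rule for deciding what counts as a confounder. Earlier in the same section it plans significance tests of the arms at baseline: "The homogeneity of the sample at the beginning of the study will be verified using Student’s t-test for independent variables", with Mann-Whitney and chi-squared alternatives.

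**The concern.** The design and the stated analysis do not meet. The plan treats Health Unit as likely to be prognostic and balances the arms on it. An analysis that follows the design carries that factor into the model, because balancing on a prognostic factor reduces the true variance of the treatment comparison. An unstratified standard error does not see that reduction.

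The wording of the adjustment points away from this. Confounding is the language of observational studies. A variable balanced across arms by design does not confound the treatment effect, so an analyst who looked for confounders would have little reason to include the unit.

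The term also fixes no particular model. The adjusted relative risk is the only analysis described for the primary outcome, and several covariate sets would satisfy the description. With researchers who know the allocation, the set should be settled before outcome data are seen.

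**Working it through.** **Step 1. Does the sample size depend on this?** Inputs from the Sample size section: a 20% difference in proportions (read as 20 percentage points), α = 0.05, power 90%, 20% loss, total 300. Assumed: two-sided test, 1:1 allocation, and a control rate, which the article does not give.

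Formula per arm: n = [1.960·√(2p̄(1−p̄)) + 1.282·√(p1(1−p1)+p2(1−p2))]² / (p2−p1)².

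For 25% against 45%, p̄ = 0.35:
- 1.960·√0.455 = 1.322
- 1.282·√0.435 = 0.845
- (1.322 + 0.845)² / 0.04 ≈ 117.4, rounded up to 118 per arm, or 236 evaluable
- 236 / 0.8 = 295

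This is close to 300. Over control rates of 20% to 60% the total runs from 273 to 325. So 300 is reproducible without any between-unit term, and carrying the unit into the model does not require more women.

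**Step 2. Effect on the standard error.** Assume seven equally sized units with rates 10%, 15%, 20%, 25%, 30%, 35% and 40%.
- Mean rate 0.25, so the variance ignoring unit is 0.25 × 0.75 = 0.1875.
- Between-unit variance: 0.05² × (9+4+1+0+1+4+9)/7 = 0.0025 × 4 = 0.0100.
- Within-unit variance: 0.1875 − 0.0100 = 0.1775.
- SE ratio, unit ignored to unit included: √(0.1875/0.1775) = 1.028.

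The standard error is overstated by about 3%. With no true effect the ratio is the same on the log relative risk scale, because both variances are divided by the same squared mean rate.

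**Step 3. Effect on type I error and power.** Simulation with 20,000 runs per setting and 240 evaluable women (300 × 0.8), 120 per arm, in seven units balanced within unit. The middle unit has a control rate of 30%. Unit logits are equally spaced from −1.5s to +1.5s around ln(0.30/0.70) = −0.847. An unstratified two-proportion z-test is compared with a Mantel-Haenszel test stratified by unit. Power is for +20 points in every unit.

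| s | Range of unit control rates | Type I error, unit ignored | Type I error, stratified | Power, unit ignored | Power, stratified |
|---|---|---|---|---|---|
| 0 | 30% in all | 0.050 | 0.050 | 0.898 | 0.896 |
| 0.3 | 21% to 40% | 0.046 | 0.049 | 0.895 | 0.898 |
| 0.6 | 15% to 51% | 0.042 | 0.051 | 0.896 | 0.907 |
| 1.0 | 9% to 66% | 0.032 | 0.052 | 0.902 | 0.934 |

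The ranges follow from 1/(1+exp(0.847 ∓ 1.5s)). Simulation error is about √(0.05 × 0.95/20,000) = 0.0015 on type I error and √(0.9 × 0.1/20,000) = 0.002 on power. Small departures of the stratified test from 0.05, and the power difference at s = 0, are therefore noise.

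**The case against.** The strongest reply is that the defect is read from silence. The article does not say that Health Unit is left out. The authors plainly regard the unit as relevant, and it could be among the unnamed factors. This is a condensed article, and the covariate list and regression family may sit in an analysis plan that is not shown. This stands to the extent that no one can claim from the article that the unit will definitely be unadjusted. It does not dispose of the point, because the criterion that is stated, confounding, is the wrong one for a stratification factor.

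A reader might also infer that the baseline tests decide which covariates enter the model, and so that type I error is distorted. The text does not say this. The tests and the adjustment appear in the same section, but no rule links them. Baseline tests are uninformative in a randomised trial, since any differences arise by chance, but removing them alone would change no result.

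The reply is also right that the cost of omitting the unit is small and in the conservative direction. The gain from adjusting for BMI and gestational age has not been shown either. Eligibility already restricts both (pre-gestational BMI 25.0 to 29.9 kg/m², gestation up to 15 weeks and 6 days), so they are offered only as examples of a fixed list.

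**Conclusion.** The point holds as a free improvement of minor severity. Randomisation is stratified by Health Unit, while the stated primary analysis does not carry that factor into the model and leaves its adjustment set open, in a trial whose researchers know the allocation.

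If the unit is left out, the confidence interval is modestly too wide and the test conservative. The standard error is about 3% too large for unit rates of 10% to 40%. Between 0 and about 3 points of power are lost over the spreads assumed, with the 3 points only at the widest. The between-unit spreads, equal unit sizes and the 30% middle rate are assumptions; the documents give no unit-level rates. The simulation compares simple tests, so it shows the direction and order of size for a regression model and not exact values.

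The documents do not support a claim that the unit is certainly omitted, that covariates are selected by baseline tests, or that leaving the unit out raises the false-positive rate.

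**What to change.** In Statistical analyses, replace the adjustment for unspecified confounders with one pre-specified primary model: the relative risk of appropriate weight gain from modified Poisson regression with robust standard errors (or log-binomial regression). The model should contain arm, Health Unit (seven levels) and a short, fixed, named list of covariates already collected at baseline, for example baseline BMI and gestational age at enrolment. State that the list is not chosen from baseline p-values or after outcome data have been seen. Present baseline characteristics by arm descriptively, without significance tests. If an analysis plan already fixes the covariates, confirm that it names Health Unit and align the article's wording with it.

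The cost is a change of wording and six degrees of freedom for the unit (7 − 1), out of about 240 evaluable women. No new data are needed and the target of 300 stays as it is.

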### Outcomes

The primary outcome of the study is adequacy of weight gain. Weight measurements will be performed by trained nutritionists in the first and second study evaluations using a portable digital scale (Tanita®, model HS 302).

The measurement made by the nutritionists up to the 13th GW will be considered as the pre-gestational weight. For the women in the 14th GW included in the study, a value of 0.45 kg will be subtracted from the measured weight and for the women in the 15th GW included in the study a value of 0.91 kg will be subtracted from their measured weight. The results of these calculations will be adopted as an estimate of pre-gestational weight. The weight measured in the second study evaluation, preferably between the 34th and 36th GW, will be considered for the calculation of weight gain, rather than the weight measured at the moment of delivery. These procedures will be adopted due to the limitations regarding the use of self-reported pre-gestational weight and due to the high variability of water retention in the late gestation period, as well as the variability of the gestational age at delivery [28].

Weight data will be obtained from all the prenatal consultations. The mean weekly weight gain will be estimated through the difference between the weight measured in the second evaluation and the first weight recorded in the second trimester of pregnancy, divided by the number of days between the evaluation dates, divided by 7. The women with mean weekly weight gain between 0.23 and 0.33 kg in the second and third trimesters of the pregnancy will be considered to present appropriate weight gain. Insufficient weight gain will be considered for those with a mean weekly weight gain of less than 0.22 kg and excessive weight gain for women with weekly weight gain of more than 0.34 kg [23].

Secondary outcomes will be: mean weekly weight gain, changes in food intake, physical activity and the biochemical profile of the pregnant women (fasting glucose, fasting insulin, total cholesterol and fractions, triglycerides and C-reactive protein), complications in the pregnancy (gestational diabetes mellitus, hypertensive disorders and prematurity), birth weight, neonatal adiposity, weight and length/height of children at 6, 12 and 24 months of age.

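### The condition for estimating the effect on neonatal adiposity and birth weight, linearity in treatment group, has no meaning with two arms and should be removed

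*Protocol article*

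**What the plan says.** The Study setting section fixes the number of groups: "This is a two-armed parallel randomized controlled trial that will be conducted among overweight, pregnant women". The Outcomes section places both endpoints among the secondary outcomes: "birth weight, neonatal adiposity, weight and length/height of children at 6, 12 and 24 months of age".

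The Statistical analyses section gives these two outcomes a paragraph of their own. It opens: "The statistical correlation method will be used to investigate the impact of the intervention on neonatal adiposity and birth weight". The next sentence sets the condition, "If there is linearity between the treatment group data and outcomes, linear regression models will be employed", and describes the model as "adopting adiposity and birth weight as the dependent variables, adjusted for potential confounders". It does not say how linearity is to be judged, or what is reported if it is judged absent.

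The same section commits to intention to treat ("The analyses of this study will follow the intention to treat principles") and closes with a general threshold ("values < 0.05 will be considered significant"). That threshold is not tied to the decision to fit the regression.

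**The concern.** The condition asks a question that a two-level variable cannot answer. An analyst who tries to apply it has only one thing to look at, namely whether outcome and arm are associated, and that is the treatment effect. If the adjusted model is fitted only when an association is visible, the published differences are a selected set and lie too far from zero on average. When no association is seen, no adjusted difference in natural units is promised.

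The abstract names the effect on neonatal adiposity as an additional aim, and the Discussion sets it beside weight gain. Readers will want a difference in grams or in adiposity units, with an interval, whichever way the result falls.

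**Working it through.** **1. Is there another between-arm analysis for these outcomes?** The remaining methods in the article do not supply one.
- The paired t-test or Wilcoxon test is for change from baseline. Birth weight and neonatal adiposity have no baseline value.
- The adjusted relative risk is for appropriate weight gain only.
- The age-adjusted models in the Discussion concern how adiposity is estimated in newborns measured after 72 h, not how the arms are compared.

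**2. Can linearity in arm fail?** Lack-of-fit degrees of freedom = levels of the predictor − parameters of the line = 2 − 2 = 0. There is nothing left with which to test linearity.

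A numerical check used one simulated data set, 120 per arm, with arm coded 0/1:
- Pearson r = 0.0591, n = 240. t = r√(n − 2)/√(1 − r²) = 0.0591 × 15.43/0.998 = 0.913 on 238 df, p = 0.362.
- The two-sample t-test gave p = 0.362 and simple linear regression gave p = 0.362.
- The regression slope was 0.1085 and the difference in means was 0.1085.
- The lack-of-fit sum of squares against the two group means was 0.

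Correlation with arm, the t-test and simple regression are thus one and the same test. The correlation step carries no information about linearity, only about the treatment effect.

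**3. What would a gate do, if one were applied?** The article gives no SD, expected effect or power figure for these outcomes, so there is no stated figure to reproduce. The Sample size section supplies only the numbers available: "a power of 90% (β = 0.1), with a 20% loss during monitoring, a sample of 300 women will be sufficient". That calculation is for the primary outcome and is not in question here.

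Inputs:
- Evaluable infants: 300 × (1 − 0.20) = 240, or 120 per arm (1:1 allocation assumed; the article states no ratio).
- Gate: two-sided p < 0.05 on the unadjusted comparison (assumed).
- True effects of 0 to 0.4 SD (assumed), normal data with SD = 1, 40,000 simulated trials for each effect.

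The standard error is √(2/120) = 0.129 SD. A difference must exceed about 1.97 × 0.129 = 0.254 SD to pass, so any true effect below that can be reported only when overestimated.

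| True effect (SD) | Passes gate | Mean estimate, all trials | Mean estimate, passing trials | Ratio to truth | 95% CI coverage, passing trials |
|---|---|---|---|---|---|
| 0 | 5% | 0.00 | 0.30 (absolute value) | – | 0% |
| 0.1 | 12% | 0.10 | 0.299 | 0.299/0.1 = 3.0 | 77% |
| 0.2 | 34% | 0.20 | 0.339 | 0.339/0.2 = 1.7 | 93% |
| 0.3 | 64% | 0.30 | 0.376 | 0.376/0.3 = 1.25 | 96% |
| 0.4 | 87% | 0.40 | 0.432 | 0.432/0.4 = 1.08 | 97% |

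With the model always fitted, the mean estimate equals the true effect and coverage is about 95% in every row.

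**The case against.** The strongest reply is that the condition, taken literally, is harmless. If linearity in a two-level variable always holds, the condition is always met, the regression is always fitted, and nothing is selected. A reader might infer from the wording that the plan makes regression depend on a significant correlation, and hence that its estimates will be biased. The article does not support that. It speaks of linearity, not significance, and its 0.05 threshold is a general statement. This part of the reply stands: the inflation figures describe one possible application of the rule, not a consequence of the text. The reply does not save the rule, because on the harmless reading the sentence is empty and the correlation step adds nothing.

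A reader might also infer that a null result would be left with no effect measure at all. That goes too far. Correlation is applied to both outcomes without condition, and a coefficient with its sample size is a standardised effect from which an interval can be derived. What remains is narrower: it is not in grams or adiposity units, and no adjusted difference is promised.

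Finally, a reader might count the unspecified confounders as a defect, or suppose that the model will adjust for variables the intervention can change, such as weight gain or gestational age at delivery. The article names no covariates for this model. Such a list is commonly left to a full protocol or analysis plan that is not shown, so its absence is no finding.

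**Conclusion.** The point holds as a defect in a rule that the article states, not as a gap. With two arms the linearity condition is either void or a data-dependent gate on the treatment effect, and the text does not settle which. That conclusion follows from the two-arm design and needs no simulation.

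The size is conditional. Inflation of about 1.7 times at 0.2 SD and 1.25 times at 0.3 SD assumes a gate at p < 0.05, 120 infants per arm and normal data. If the regression is in fact always fitted, the inflation is nil.

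Severity is moderate. The rule governs two secondary outcomes, one of which the article gives some prominence. The relative-risk analysis of appropriate weight gain and the sample size are not affected.

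**What to change.** Delete the correlation step and the linearity condition. In their place, state that birth weight and neonatal adiposity will each be analysed by linear regression on randomised arm in all cases, adjusted for Health Unit (the stratification factor in the Allocation section) and for pre-specified covariates fixed before randomisation only. Report the adjusted mean difference, in grams or in adiposity units, with its 95% CI whatever its size or p-value.

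The cost is a change of wording, made before the data are analysed. It needs no new data, visits or participants.

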## Discussion

This clinical trial will be unprecedented due to investigating the effectiveness of a nutritional intervention strategy based on encouraging the consumption of fresh or minimally processed foods and physical activity in overweight, pregnant women for appropriate weight gain and neonatal adiposity. Additional investigations will include changes in dietary intake and physical activity, changes in the biochemical profile of the pregnant women (fasting glucose, fasting insulin, total cholesterol, cholesterol fractions, triglycerides and C-reactive protein), pregnancy complications (GDM, hypertensive disorders and prematurity), birth weight, and weight and length/height of the children at 6, 12 and 24 months of age.

Although promising results regarding appropriate weight gain in overweight, pregnant women have recently been demonstrated by LIFE-MOMs [10], the number of investigations into the impact of intervention measures adapted to the usual conditions of public health systems of countries of low and medium development is still considered insufficient [9]. Furthermore, increasing evidence from observational studies suggests deleterious effects on the health of adults and pregnant women due to the high consumption of ultra-processed products [13–19].

Only one previous clinical trial investigated the effect of unprocessed food consumption on weight control in adults [21]. In the study by Hall and colleagues [21], all meals were provided to the study participants, who did not face obstacles related to food acquisition and preparation, steps necessary to adopt a diet based on the consumption of fresh or minimally processed food. In addition, ultra-processed products are widely offered through various marketing and advertising strategies, which influence the food choices of free living individual [12, 20]. Accordingly, the present study could advance our knowledge regarding the effectiveness of such a strategy.

The fact that the study is unprecedented and the feasibility of the implantation of the strategy in public health services of countries of low and medium development can be considered important strengths. In addition, all the assessments will be made by trained nutritionists to ensure the quality control of the data. As all the study evaluations will be conducted in Primary Care Units, the evaluation of some newborns will be conducted after 72 h, which may affect the estimation of adiposity. To minimize this limitation, age-adjusted models will be employed [41]. We believe the results of the study will expand the knowledge regarding the effect on maternal and child health of an intervention based on the degree of food processing and on encouraging the practice of physical activity.

## Data Availability

Datasets arising from the study might be available upon reasonable request from the corresponding author: [contact]

